**Adequate Clinical and Parasitological Response (ACPR)**

- Absence of parasitemia on day 28 or 42 irrespective of axillary temperature without previously meeting any of the criteria of Early Treatment Failure or Late Clinical Failure or Late Parasitological Failure

In order to differentiate a recrudescence (same parasite strain) from a newly acquired infection (different parasite strain), a genotypic analysis based on merozoite surface protein-1 (*msp1)*, merozoite surface protein 2 (*msp2)* and glutamate-rich protein (*glurp)* will be performed by PCR for Pf. Additionally, we will characterize microsatellite markers for Pf to differentiate recrudescence from reinfection and potentially assess for drug resistance markers.

**Definition of Treatment Outcomes for *P. vivax* infections, WHO 2002** [4]

Treatment failure defined as:

1. Clinical deterioration due to *P. vivax* illness requiring hospitalization in presence of parasitemia
2. Presence of parasitemia and axillary temperature ≥37.5oC any time between Day 3 and Day 28 or 42
3. Presence of parasitemia on any day between day 7 and day 28 or 42, irrespective of clinical conditions.

*P. vivax* infections that recur after drug treatment can have 1 of 3 etiologies: 1) recrudescence, 2) reinfection, or 3) relapse arising from the dormant liver stage (hypnozoites). In order to differentiate the treatment failures as recrudescence or relapse from a newly acquired infection, a genotypic analysis based on P. vivax circumsporozoite protein (*pvcs*), the merozoite surface protein 1 (*pvmsp1*) and the merozoite surface protein 3-alpha (*pvmsp3-alpha*) will be performed by PCR for Pv. Additionally, we also will characterize microsatellite markers to assess recrudescence from reinfection and for drug resistance markers. Those who fail in the vivax arms will have drug levels tested from the already collected filter paper.

**Valid end-points** include treatment failure, completion of the follow-up period without treatment failure, loss to follow-up, withdrawal from study (voluntary or involuntary, and protocol violation). Loss to follow-up occurs when, despite all reasonable effort, an enrolled patient who does not attend the scheduled visits, cannot be found. Patients who withdraw from the study during the treatment period (days 0-2) will be treated with AL or CQ depending on the species according to the national policy. They will be referred back to the clinic to continue with care.

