**Criteria for withdrawal**

Patients meeting any of the following criteria will be withdrawn:

- Withdrawal of consent
- Failure to complete the treatment
- Vomiting both initial and replacement doses at any single time in the treatment (i.e. If the patient vomits both attempts to administer the morning dose that would require withdrawal; however, vomiting the initial morning dose but not the morning replacement dose would not require withdrawal), persistent vomiting
- Severe side-effects necessitating hospitalization
- Progression to severe malaria
- Occurrence during the follow-up of concomitant disease that would interfere with a clear classification of the treatment outcome
- Antimalarial (or antibiotics with antimalarial activity) treatment administered by a third party or self-medication with antimalarial (or antibiotics with antimalarial activity) assessed by asking participants or their caretaker at follow-up visits
- Detection of another malaria species infection during the follow-up
- Erroneous inclusion of a patient outside of the inclusion/exclusion criteria
- Misclassification of a patient due to a laboratory error (parasitemia) leading to the administration of the rescue treatment

**Training for personnel**: Clinicians and laboratory personnel are trained and licensed in Ethiopia. In addition, they will receive approximately 1 week additional training to review the protocol of this study. In addition to technical aspects of specific laboratory techniques and clinical assessments, training will stress the importance of confidentiality, appropriate techniques for obtaining informed consent, Staff will participate in practical exercises. Continued appropriate behavior with regard to informed consent will be reinforced by intermittent observation by the supervisor. The staff will include 1-2 laboratory technicians for microscopy, and 1-2 staff persons for enrollment and clinical assessments.

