**EMERGENCY CARE**

Any patient with treatment failure or recrudescence will receive quinine 10mg/kg/dose every 8 hours for 7 days. This will be given orally unless the patient has persistent vomiting, in which case it will be given IM/IV until the vomiting resolves and then will be switched to oral therapy.

Patients with signs of severe malaria (altered mental status, coma, convulsions, hemoglobin <5g/dl, Respiratory distress, circulatory collapse, or abnormal bleeding), persistent vomiting or severe side effects will be hospitalized and receive parenteral therapy with quinine and relevant supportive treatments, according to National Guidelines.

Any participant who develops urticaria or difficulty breathing following administration of the treatment drug will be treated with diphenhydramine or chlorpheniramine and will be withdrawn from the study. In addition, patient and or their parents, caretakers and family members will be counseled that the patient should not receive additional doses of the antimalarial they were given. These patients will be treated with oral quinine for seven days as per the rescue protocol.

Adult patients and parents with children in the study will be encouraged to return to the clinic for any fever or other signs of illness on any day during the 42 day follow-up period, allowing for early detection and treatment of illness before it becomes severe.

Any hospitalization which occurs during the 42 day follow-up period will be paid for by the study.

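### The treatment rule for withdrawals on days 0-2 has no stated limits and overlaps with a different rule in Emergency Care for patients withdrawn for allergy, persistent vomiting, severe side effects or severe malaria

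*Protocol*

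**What the plan says.** Four places in the protocol bear on what happens to a patient who leaves the study during dosing.

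- **End-points, Valid end-points paragraph.** One of the listed end-points is "withdrawal from study (voluntary or involuntary, and protocol violation". Shortly after comes the treatment rule: "Patients who withdraw from the study during the treatment period (days 0-2) will be treated with AL or CQ depending on the species". The sentence ties this to national policy, and the next one refers these patients back to the clinic for further care. No type of withdrawal is exempted.
- **Criteria for withdrawal.** The list includes "Severe side-effects necessitating hospitalization" and "Progression to severe malaria". Persistent vomiting is added at the end of the item on vomited doses: "would not require withdrawal), persistent vomiting".
- **Emergency Care.** A participant with urticaria or difficulty breathing after the study drug "will be treated with diphenhydramine or chlorpheniramine and will be withdrawn from the study". Patient and family are told that no more of that antimalarial should be taken, and then: "These patients will be treated with oral quinine for seven days as per the rescue protocol". Separately, patients with signs of severe malaria, "persistent vomiting or severe side effects will be hospitalized and receive parenteral therapy with quinine".
- **Methods to Minimize Risks.** This repeats the withdrawal for urticaria or difficulty breathing but does not mention quinine. Its counselling is worded as avoiding other antimalarials, whereas Emergency Care refers to the one already given.

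**The concern.** For a patient withdrawn on days 0-2 because of a reaction or clinical deterioration, the protocol gives two instructions that differ in both drug and destination. Neither section refers to the other or says which takes precedence. Staff who look up withdrawal under End-points find only AL or CQ and a return to the clinic; staff who look under Emergency Care find quinine and, for some patients, hospital.

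The overlap falls where drug reactions are most likely. Annex V schedules study drug on days 0, 1 and 2 only, and the adverse-events section says that most severe allergic reactions show within an hour of a dose. For some allergic patients, the literal End-points rule names the very drug that Emergency Care says they should not take again. What is at stake is participant safety and consistent handling across sites.

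**Working it through.** The point concerns two text rules, so the main check is to apply both to each kind of patient withdrawn on days 0-2.

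Inputs: under Intervention or treatment, all falciparum patients receive AL and vivax patients are assigned AL or CQ. Under Drugs, CQ is the nationally recommended drug for vivax and AL for falciparum.

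| Patient withdrawn on days 0-2 | Valid end-points rule | Emergency Care rule | Result |
| --- | --- | --- | --- |
| Falciparum on AL, urticaria or difficulty breathing | AL | No further AL; oral quinine | Conflict; barred drug repeated |
| Vivax on CQ, urticaria or difficulty breathing | CQ | No further CQ; oral quinine | Conflict; barred drug repeated |
| Vivax on AL, urticaria or difficulty breathing | CQ (by species, under national policy) | No further AL; oral quinine | Conflict; a different drug, but not quinine |
| Any arm, persistent vomiting or severe side effects needing hospitalization | AL or CQ by species; clinic | Hospital; parenteral quinine | Conflict in drug and destination |
| Any arm, signs of severe malaria | AL or CQ by species; clinic | Hospital; parenteral quinine | Conflict in drug and destination |
| Any arm, initial and replacement doses both vomited, vomiting not persistent | AL or CQ by species; clinic | Not named | No direct conflict |

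Emergency Care itself states withdrawal only for the allergic patients. In the fourth and fifth rows, withdrawal status comes from Criteria for withdrawal, so those conflicts need three sections read together.

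For size, the only relevant rate is in the adverse-events section: 6 anaphylactic-type reactions in 17,000 artemisinin recipients, that is 17,000/6 = 2,833, or 1 in 2,833, with a 95% interval of 1 in 1,362 to 1 in 6,944. The sample-size section plans 120 patients per arm; AL is used in two arms, so 2 × 120 = 240.

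- Expected number: 240/2,833 = 0.08, about 0.1.
- At the interval limits: 240/6,944 = 0.03 and 240/1,362 = 0.18.

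This covers anaphylactic-type reactions to AL only. The protocol gives no rate for urticaria alone, for reactions to CQ, or for withdrawal because of persistent vomiting, severe side effects or severe malaria, so no total is calculated.

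For the analysis, the data analysis plan excludes withdrawn patients from the per-protocol analysis and keeps them in the survival analysis until the last day before drop-out. Neither depends on the treatment given after withdrawal.

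**The case against.** The strongest reply is that the Valid end-points sentence was meant only for patients who choose to leave partway through a course. It uses the active voice, whereas other sections describe patients being withdrawn by the study. A referral back to the clinic fits someone who leaves by choice better than someone in hospital, and Anticipated Benefits describes a patient's right to ask for transfer to the regular clinic. The phrase about voluntary or involuntary withdrawal sits in the list of end-points, not in the treatment sentence. A specific emergency rule would also normally override a general one. Finally, the sentence defers to national policy, and Justification of exclusion criteria provides an alternative drug under national guidelines for known sensitivity.

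This may well be the intention, but the protocol does not say so. The active and passive wording is not a reliable guide, because Criteria for withdrawal lists withdrawal of consent among the reasons for which patients will be withdrawn. No order of precedence is stated. The treatment sentence names only AL or CQ, and the guidelines it relies on are not part of the document.

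Some of the reply stands. Severe malaria on days 1-3 with parasitemia is also an Early Treatment Failure. It therefore has its own route to quinine under Rescue Treatment and to alternative treatment in Annex VI, so the practical risk of confusion there is smaller.

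A reader might also infer that the protocol re-exposes every patient withdrawn for intolerance to the drug that caused it. The documents do not support that. Emergency Care expressly bars repetition after an allergic reaction, a vivax patient on AL would move to CQ even under the End-points rule, and vomiting of both doses is not covered by Emergency Care unless it is persistent. Nor do they support a guess that a few per cent of all participants would be affected.

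**Conclusion.** The point holds as an unresolved overlap between two rules. Read as written, the End-points rule and Emergency Care give different instructions for patients withdrawn on days 0-2 for urticaria or difficulty breathing, persistent vomiting, severe side effects or severe malaria. For two of the three combinations of species and drug, the literal End-points rule also repeats, after an allergic reaction, the drug that Emergency Care bars.

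Few patients are likely to meet the conflict, and the allergic cases in particular should be rare. That figure assumes that 120 patients are enrolled per arm and that the quoted artemisinin rate applies to AL. The numbers for the other reasons are unknown.

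The conclusion rests on the absence of any stated limit or precedence, not on a claim about what the investigators intended. No efficacy estimate, analysis set or sample size is affected. The point deserves correction because it concerns participant safety and the remedy is simple.

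**What to change.** Reconcile the Valid end-points paragraph, Criteria for withdrawal, Emergency Care and Methods to Minimize Risks so that each type of withdrawal falls under exactly one treatment rule.

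- In Valid end-points, state which withdrawals on days 0-2 the AL-or-CQ rule covers, and refer to Emergency Care for the others.
- State which rule applies when initial and replacement doses are both vomited but vomiting is not persistent.
- Say how early severe malaria, which is both a withdrawal criterion and an Early Treatment Failure, is routed.
- Align the counselling and follow-on treatment wording in Methods to Minimize Risks with Emergency Care.

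Which treatment each group receives is for the investigators to decide. The main change is one sentence in Valid end-points, with small wording edits elsewhere. It costs no sample size and no change to the analysis.

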**Criteria for withdrawal**

Patients meeting any of the following criteria will be withdrawn:

- Withdrawal of consent
- Failure to complete the treatment
- Vomiting both initial and replacement doses at any single time in the treatment (i.e. If the patient vomits both attempts to administer the morning dose that would require withdrawal; however, vomiting the initial morning dose but not the morning replacement dose would not require withdrawal), persistent vomiting
- Severe side-effects necessitating hospitalization
- Progression to severe malaria
- Occurrence during the follow-up of concomitant disease that would interfere with a clear classification of the treatment outcome
- Antimalarial (or antibiotics with antimalarial activity) treatment administered by a third party or self-medication with antimalarial (or antibiotics with antimalarial activity) assessed by asking participants or their caretaker at follow-up visits
- Detection of another malaria species infection during the follow-up
- Erroneous inclusion of a patient outside of the inclusion/exclusion criteria
- Misclassification of a patient due to a laboratory error (parasitemia) leading to the administration of the rescue treatment

**Training for personnel**: Clinicians and laboratory personnel are trained and licensed in Ethiopia. In addition, they will receive approximately 1 week additional training to review the protocol of this study. In addition to technical aspects of specific laboratory techniques and clinical assessments, training will stress the importance of confidentiality, appropriate techniques for obtaining informed consent, Staff will participate in practical exercises. Continued appropriate behavior with regard to informed consent will be reinforced by intermittent observation by the supervisor. The staff will include 1-2 laboratory technicians for microscopy, and 1-2 staff persons for enrollment and clinical assessments.

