**Classification of Treatment Outcomes, WHO 2003**

**Early Treatment Failure (ETF)**

- Development of danger signs or severe malaria on day 1, day 2 or day 3 in the presence of parasitemia
- Parasitemia on day 2 higher than day 0 count irrespective of axillary temperature
- Parasitemia on day 3 with axillary temperature ≥37.5 ºC
- Parasitemia on day 3 ≥25% of count on day 0

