**Late Treatment Failure (LTF)**

***Late Clinical Failure* (LCF)**

- Development of danger signs or severe malaria after day 3 in the presence of parasitemia, without previously meeting any of the criteria of Early Treatment Failure
- Presence of parasitemia and axillary temperature ≥37.5 ºC or history of fever on any day from day 4 to day 28 or 42, without previously meeting any of the criteria of Early Treatment Failure

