# DATA HANDLING AND ANALYSIS

**Data analysis plan, including statistical methodology and planned tables and figures**

SAS 9.1 (Cary, NC) as well as the WHO drug efficacy tools provided at <http://www.who.int/malaria/toolsformonitoring.html> will be used for data management and analysis. Data will be analyzed using two methods: **per protocol analysis**, where patients who were withdrawn from the study or who were lost to follow-up are excluded, and **survival analysis**, where all enrolled patients are included in the analysis until the last day before drop-out. In addition to voluntary withdrawals or treatment non-compliance, patients will be considered for the analysis as withdrawn if the PCR results are unclassifiable.

The final analysis will include:

- A description of the patients screened, and the distribution of the reasons for exclusion.
- A description of the patients included in the study.
- The proportion of patients lost to follow-up or withdrawn and the distribution of reasons for withdrawal.
- The PCR-adjusted and unadjusted proportion of ETF, LCF, LPF, and ACPR in the Pf arm at day 28 and day 42 with 95% confidence intervals using both methods of analysis.
- Both drug-level and PCR-adjusted and unadjusted proportion of treatment failures in each Pv arm at day 28 and day 42 with 95% confidence intervals using both methods of analysis
- Frequency of side effects, severe malaria, anemia, and hospitalizations by treatment arm

**Data collection**: Data will be collected and recorded at the health facility by one of the trained staff members. All data entry forms will be checked for completeness. Laboratorians may complete brief reports on laboratory findings to share with clinicians who will transfer these results to the case report form of the appropriate patient, the laboratory results will be entered into an Excel database.

**Information management and analysis software:** Microsoft Excel (Redmond, Washington) will be used for double entry of laboratory data and clinical data. SAS 9.1 (Cary, NC) will be used for data analysis.

**Data entry, editing, handling, storage and disposition**: Some open-ended data including the names of specific drugs or diagnoses will be coded prior to data entry. A list of standard codes for these fields will be developed by hand once collection of data is complete. All forms will then be coded and checked by 2 different team members.

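### Severe malaria with parasitemia in P. falciparum is both a treatment failure and a ground for withdrawal, and the protocol does not say which classification prevails

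*Protocol*

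**What the plan says.** All references are to the protocol.

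- **Failure, P. falciparum.** Under Classification of Treatment Outcomes, the first early treatment failure (ETF) criterion is "Development of danger signs or severe malaria on day 1, day 2 or day 3 in the presence of parasitemia". The first late clinical failure (LCF) criterion begins "Development of danger signs or severe malaria after day 3 in the presence of parasitemia". Annex I repeats both.
- **Failure, P. vivax.** The definition of vivax outcomes, repeated in Annex II, does not use the term severe malaria. Its first criterion is clinical deterioration from vivax "illness requiring hospitalization in presence of parasitemia". The EMERGENCY CARE section supplies the link: patients with signs of severe malaria, "persistent vomiting or severe side effects will be hospitalized and receive parenteral therapy with quinine".
- **Withdrawal.** Criteria for withdrawal opens with "Patients meeting any of the following criteria will be withdrawn", and the list includes "Progression to severe malaria". It makes no exception for a patient who already meets a failure criterion.
- **Analysis.** DATA HANDLING AND ANALYSIS names two methods: a per-protocol analysis, "where patients who were withdrawn from the study or who were lost to follow-up are excluded", and a survival analysis, "where all enrolled patients are included in the analysis until the last day before drop-out".
- **Precedence.** The paragraph on valid end-points names failure and withdrawal as separate end-points and ranks neither above the other. The failure categories are ordered among themselves (LCF requires no earlier ETF; late parasitological failure requires neither), but failure is not ordered against withdrawal.

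**The concern.** The event that defines the failure also triggers the withdrawal. If withdrawal prevails, a patient leaves the failure count because of the outcome being measured. That exclusion, or censoring, is informative. It can only raise the efficacy estimate, and it removes the most serious failures.

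Efficacy is the primary outcome in every arm, and the results are meant to inform national treatment guidelines. The study is open-label, so an unstated choice between the two classifications would be made by staff who know the treatment. This is not a detail left for a statistical analysis plan: the protocol itself fixes the outcome definitions, the withdrawal list and the handling of withdrawn patients, and these disagree.

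**Working it through.** **Step 1: one patient, two rules.** Take a P. falciparum patient with parasitemia who develops severe malaria.

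| Rule applied | Days 1–3 | After day 3 |
|---|---|---|
| Outcome classification | ETF | LCF |
| Withdrawal list, then per-protocol analysis | excluded from numerator and denominator | same |
| Withdrawal list, then survival analysis | censored before the event, if withdrawal counts as drop-out | same |

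In the survival analysis the person-time is kept but the event is lost.

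**Step 2: the plan's own figures.** The sample-size section gives 120 per arm, 20% loss to follow-up, an assumed ACPR of 90% and an exact 95% interval of 82.4% to 95.1%. The exact (Clopper-Pearson) interval for 90/100 is 82.4% to 95.1%, so the figure reproduces with 100 evaluable patients. A 20% loss from 120 leaves 120 × 0.8 = 96. I use 96 below; nothing here depends on the difference.

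**Step 3: per-protocol effect.** Let N be the evaluable patients, F the true failures, and s the failures that are severe and withdrawn. Then ACPR(s) = (N − F)/(N − s). The protocol gives no rate of severe malaria, so s is an assumption.

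Near the planning value, N = 96 and F = 10:

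| s | ACPR | Exact 95% interval |
|---|---|---|
| 0 | 86/96 = 89.6% | 81.7–94.9 |
| 1 | 86/95 = 90.5% | 82.8–95.6 |
| 2 | 86/94 = 91.5% | 83.9–96.3 |
| 3 | 86/93 = 92.5% | 85.1–96.9 |

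The sample-size section also says that reported failure is at most 5%. With F = 5, ACPR is 91/96 = 94.8% at s = 0, 91/94 = 96.8% at s = 2 and 91/93 = 97.8% at s = 3. In the s = 2 case the failure estimate falls from 5/96 = 5.2% to 3/94 = 3.2%.

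**Step 4: survival effect.** Assume 120 enrolled, 12 failures and no other loss. Counted as events, the estimate is 108/120 = 90.0%. If the s severe cases are censored before every other failure, it is 108/(120 − s): 90.8%, 91.5% and 92.3% for s = 1, 2 and 3. If they are censored after every other failure, it is (108 + s)/120: 90.8%, 91.7% and 92.5%. Either way the shift is about 0.8 point per case.

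**The case against.** The strongest reply is that failure is meant to come first. END-POINTS says that all P. falciparum patients receive one of the four outcome categories. The failure criteria have no carve-out for withdrawal, and if withdrawal always won, their severe-malaria part could never count in the per-protocol analysis. Failure is also named first among the valid end-points. This is a plausible reading, and it stands to this extent: a reader might infer that both planned analyses will overstate efficacy, and the documents do not support that as a certainty. They support a conflict that biases efficacy if the withdrawal rule is applied as worded. The failure-first reading is nowhere stated, and the withdrawal wording is mandatory.

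Other replies:

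- **Drop-out is not defined.** The protocol does not say that the term covers a patient who has just met a failure criterion, so loss of the event in the survival analysis is one reading. This stands.
- **The cases would still be visible.** Reasons for withdrawal are to be tabulated, as is the frequency of severe malaria and hospitalization by arm. This is partial mitigation, because those tables do not feed the failure proportions.
- **The vivax overlap is indirect.** It runs through hospitalization, and the severe-malaria table in Annex III is headed for P. falciparum. This stands: a reader might infer the same direct contradiction in the vivax arms, but the text does not contain one.
- **The number of cases is small.** Enrollment excludes danger signs and severe malaria, caps P. falciparum density at 100,000 per μl, and is followed by visits on days 1 to 3. The planned interval is 95.1 − 82.4 = 12.7 points wide, against about 1 point per case. This limits the size. It does not remove a bias that runs in one direction, which the interval does not cover.

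**Conclusion.** The contradiction is in the current text and nothing in the protocol resolves it. It is direct for P. falciparum and indirect for P. vivax. Read literally, the withdrawal and analysis rules push efficacy upward by about 1 percentage point per affected patient in the per-protocol analysis (96 evaluable, 10 failures) and about 0.8 point in the survival analysis (120 enrolled, 12 failures, no other loss). The number of affected patients is an assumption, since no rate of severe malaria is given, and it is probably small.

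A reader might attach meaning to the estimate passing 90%, as it does with a single case in the per-protocol table. The documents do not support this: 90% is the planning value for sample size, not a decision threshold. Nor do they show that the withdrawal criterion itself is misplaced. It governs participation; only the outcome classification is in conflict.

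**What to change.** Reconcile the P. falciparum and P. vivax outcome definitions (END-POINTS, Annexes I and II) with Criteria for withdrawal and the data analysis plan. Add one sentence to the analysis section to this effect: failure criteria are applied before withdrawal criteria, and a patient who meets a failure criterion is counted as a failure on that day in both the per-protocol and the survival analysis, whatever then happens to study participation. A cross-reference from the withdrawal list would help.

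The withdrawal list need not change, and neither does clinical care. The cost is one sentence and no new data, provided it is settled before outcomes are classified.
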